**Table S1. Definition of primary and secondary outcome measures**

| **Outcome** | **Definition** |
| --- | --- |
| *Short-term outcomes* | |
| Time alive and free of inotropes/vasopressors *(primary outcome)* | Defined as the duration in days alive and free of inotropes/vasopressors (dopamine, dobutamine, adrenaline, noradrenaline, milrinone, or vasopressin) in the first 7 days post randomisation; patients dying within 7 days of randomisation will be assigned a value of zero. The following continuous infusions will be considered as inotropes/vasopressors: adrenaline, noradrenaline, dopamine, dobutamine, vasopressin, milrinone. |
| Alive and free of multi-organ dysfunction at 72 hours post-randomisation | Composite binary outcome measure of multi-organ dysfunction and survival status at 72 hours post-randomisation. Multi-organ dysfunction is defined as a pSOFA* (pediatric Sequential Organ Failure Assessment) organ-specific subscore increase in at least 2 organs from baseline within 72 hours of randomisation. Patients discharged from PICU prior to 72 hours post-randomisation will be considered to have no organ dysfunction at the 72 hour timepoint, presuming the patient is alive. Denominator is number of enrolled patients. |
| PICU-free survival | Duration of days alive and free from PICU admission, censored at 28 days post-randomisation. Patients dying within 28 days of randomisation will be censored as zero days to correct for the competing effect of mortality on PICU length of stay. Length of PICU stay for patients re-admitted to PICU within the same hospital admission and within 28 days of randomisation will be added to the index length of stay. |
| Survival free of organ support | Duration of days alive and free from invasive ventilation, inotropes/vasopressors, extracorporeal membrane oxygenation (ECMO), and renal replacement therapy, censored at 28 days post-randomisation. Patients dying within 28 days of randomisation will be recorded as zero days. |
| Survival free of cardiovascular support | Duration of days alive and free from inotropes/vasopressors and ECMO, censored at 28 days post-randomisation. Patients dying within 28 days of randomisation will be recorded as zero days. |
| Survival free of ventilation | Duration of days alive and free from invasive ventilation, censored at 28 days from randomisation. Patients dying within 28 days of randomisation will be recorded as zero days. |
| Day 28 mortality | Death occurring within 28 days of randomisation. Denominator is number of enrolled patients. |
| PICU length of stay | Measured as days from randomisation to PICU discharge, censored at 28 days post-randomisation. Deaths occurring within 28 days post-randomisation will be censored at time of death. Length of PICU stay for patients re-admitted to PICU within the same hospital admission and within 28 days of randomisation will be added to the index length of stay. |
| Hospital length of stay | Measured as days from randomisation to hospital discharge, censored at 28 days post-randomisation. Only the index hospital admission will be included (i.e. if there are subsequent hospital admissions within 28 days post-randomisation, the length of stay of such admissions will not contribute to the outcome). Deaths occurring within 28 days post-randomisation will be censored at time of death. |
| Hyperglycaemia within 7 days of randomisation | Treated with intravenous insulin for high blood glucose or higher than usual requirement of insulin dose (if a known diabetic) within 7 days of randomisation. |
| Hypoglycaemia within 7 days post-randomisation | Blood glucose level <2.6 mmol/L within 7 days post-randomisation. |
| Hypernatraemia within 7 days post-randomisation | Serum sodium >155 mmol/L within 7 days post-randomisation |
| Hospital-acquired microbiologically confirmed infection within 28 days post-randomisation | Hospital-acquired microbiologically confirmed infection within 28 days post-randomisation. |
| Oxalate nephropathy within 28 days post-randomisation | As reported by treating medical team within 28 days post-randomisation |
| Haemolysis within 7 days post-randomisation | As reported by the treating medical team within 7 days post-randomisation, and if not explained by other factors such as ECMO. |
| Worsening of liver function within 7 days post-randomisation | >2x increase in Alanine Transferase (ALT) from baseline to day 7 post-randomisation and/or an increase in total bilirubin of more than 68 micromol/L from baseline to day 7 post-randomisation. |
| Costs | Total direct healthcare costs for the index hospital admission, including PICU and ward bed-days, organ-support therapies, investigations, and medication use. Costs will be derived using standardised unit cost estimates for Australian sites. |
| *Long-term outcomes* | |
| Health-related quality of life | Utility weight at 6 months derived from the Pediatric Quality of Life Inventory (PedsQL) scores using a validated mapping algorithm. |
| Quality-adjusted life years (QALYs) | Patient-level QALYs calculated from survival and health state utilities between randomisation and 6 months post-randomisation. |
| Total healthcare costs to 6 months | Sum of index hospitalisation costs and post discharge healthcare utilisation collected at 6-month follow-up. |
| Functional status 6 months post-randomisation | 1. Change in Functional Status Score (FSS) from baseline to 6 months post-randomisation. Participants without a recorded FSS at baseline but who have a score at 6 months will not be included in the calculation of the outcome measure, but will have their 6 month FSS reported descriptively. 2. Modified Paediatric Overall Performance Category^ (combined Paediatric Overall Performance Category and Modified Glasgow Outcome Score) at 6 months post-randomisation, with categories grouped as good/normal/functionally normal, mild disability, moderate/severe disability, coma/vegetative state, brain death. |
| Neurodevelopmental vulnerability at 6-months post-randomisation | A binary indicator of impairment if, in any of the following assessments relevant for age of the child, impairment is indicated (identified as developmental assessment >1 SD below the normative mean, or exceeding specified impairment cutoffs, as per assessment guidance):   - Pediatric Quality of Life Inventory (PedsQL) Total Score; - Ages and Stages Questionnaire, 3rd Edition (ASQ-3) Domain Scores OR Strengths and Difficulties Questionnaire (SDQ) Total Difficulties Score; - Pediatric Emotional Distress Scale (PEDS) Total Score OR Children’s Revised Impact of Events Scale (CRIES-13) Total Score; - Behavior Rating Inventory for Executive Function (BRIEF-2) Global Executive Composite Score OT Behavior Rating Inventory for Executive Function for Pre-schoolers (BRIEF-P) Global Executive Composite Score.   Assessments are completed in the order presented in the preceding sentence, aligned with order of importance. The primary analysis will use only complete assessment data (i.e. completion of all age relevant assessments). A sensitivity analysis will include patients with at least PedsQL completed, assuming that if a participant does not have complete data for any individual assessment, there will be no vulnerability assumed in that domain. Individual components of this outcome will also be presented; this is particularly relevant for PedsQL which was the only tool completed by participants recruited from Brazilian sites. |

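### The hypernatraemia and hypoglycaemia rows of Table S1 have no new-onset rule, so an abnormality that predates randomisation and persists counts as an event and usually dilutes these two risk ratios

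*SAP*

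**What the plan says.** SAP Table S1 sets out the outcome definitions. The checklist in S3 (items 26a to 26c) refers to that table for the specification, measurement and derivation of every outcome.

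- Hypernatraemia: "Serum sodium >155 mmol/L within 7 days post-randomisation".
- Hypoglycaemia: "Blood glucose level <2.6 mmol/L within 7 days post-randomisation".

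Both are complete rules with a cut-off and a window. Neither asks for a baseline value inside the limit, for new onset or for worsening.

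Other rows of the same table do refer to the child's starting point or to another cause:

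- Worsening of liver function uses ">2x increase in Alanine Transferase (ALT) from baseline to day 7 post-randomisation", or a stated rise in bilirubin over the same interval.
- Multi-organ dysfunction at 72 hours uses a pSOFA "organ-specific subscore increase in at least 2 organs from baseline within 72 hours of randomisation".
- Haemolysis is reported by the treating team "and if not explained by other factors such as ECMO".

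The effect measure for harms is not in the text at hand. The S3 checklist places harms on page 15 and analysis methods on pages 11 to 13 of the main SAP.

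**The concern.** Children in septic shock may have a deranged sodium or glucose before they are randomised. Under these two rows, a derangement that is still present in the first later sample is recorded in the same way as one that arises on treatment. The count then mixes two things: new events, which treatment may cause, and old abnormalities that have not yet resolved.

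These are safety outcomes. If the old abnormalities are spread evenly over the arms and persist equally, they add similar numbers of events to each arm. The ratio shrinks and noise increases, so a real excess of new events in a drug arm is harder to see. If treatment affects how long an existing abnormality lasts, the recorded ratio cannot tell that effect from new harm.

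**Working it through.** The text at hand gives no event rate, baseline prevalence or arm size for these outcomes, so there is no figure of the plan to reproduce. All inputs below are assumptions, chosen to show a range.

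**Inputs**
- b: share of children beyond the threshold at randomisation, 2%, 5% or 10%, equal in all arms.
- r0, r1: risk of a new event in the control and treated arm.
- s0, s1: probability that an existing abnormality is still beyond the threshold in a later sample, by arm.
- n: 130 children per arm, for power only.

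**Recorded risk in each arm:** q = b × s + (1 − b) × r.

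**Step 1. Full, equal persistence (s0 = s1 = 1), r0 = 5%, r1 = 10%, true ratio 2.00**

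| b | q0 | q1 | Ratio | Difference |
|---|---|---|---|---|
| 2% | 0.02 + 0.98 × 0.05 = 0.0690 | 0.02 + 0.98 × 0.10 = 0.1180 | 1.71 | 0.0490 |
| 5% | 0.05 + 0.95 × 0.05 = 0.0975 | 0.05 + 0.95 × 0.10 = 0.1450 | 1.49 | 0.0475 |
| 10% | 0.10 + 0.90 × 0.05 = 0.1450 | 0.10 + 0.90 × 0.10 = 0.1900 | 1.31 | 0.0450 |

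Counting new events only among children at risk gives back 2.00. The risk difference equals (1 − b) × (r1 − r0), so it falls only from 0.0500 to between 0.0490 and 0.0450.

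**Step 2. Partial, equal persistence.** Full persistence is the worst case for dilution. At b = 2%:
- s = 0.5: (0.010 + 0.098) / (0.010 + 0.049) = 0.108 / 0.059 = 1.83.
- s = 0.25: (0.005 + 0.098) / (0.005 + 0.049) = 0.103 / 0.054 = 1.91.

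**Step 3. Power at full persistence.** Two-sided 5%, normal approximation, with m = (q0 + q1)/2:

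power = Φ{[(q1 − q0)√n − 1.96√(2m(1 − m))] / √[q0(1 − q0) + q1(1 − q1)]}

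The rows as written use the recorded risks with n = 130. The new-onset comparison uses r0 and r1 with n = 130 × (1 − b).

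Example at b = 5%, 5% v 10%: as written, (0.542 − 0.905) / 0.460 = −0.79, power 22%. New-onset with n = 123.5, (0.556 − 0.730) / 0.371 = −0.47, power 32%.

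| New-onset risks | b | As written | New-onset |
|---|---|---|---|
| 5% v 10% | 2% | 27% | 33% |
| 5% v 10% | 5% | 22% | 32% |
| 5% v 10% | 10% | 16% | 31% |
| 5% v 15% | 2% | 69% | 76% |
| 5% v 15% | 5% | 59% | 75% |
| 5% v 15% | 10% | 46% | 73% |

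**Step 4. Persistence that differs by arm.** Take b = 5%, r0 = 5% and a true new-event ratio of 1.5, so r1 = 7.5%.
- s0 = s1 = 0.5: (0.025 + 0.07125) / (0.025 + 0.0475) = 1.33.
- s0 = 0.5, s1 = 0.9: (0.045 + 0.07125) / (0.025 + 0.0475) = 1.60.
- s0 = 0.9, s1 = 0.5: (0.025 + 0.07125) / (0.045 + 0.0475) = 1.04.

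The recorded ratio can thus lie below or above 1.5. With no effect on new events and equal persistence it is 1.00, so no false harm arises on average.

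**The case against.** **Any occurrence in a fixed window is a legitimate definition.** Hypernatraemia and hypoglycaemia are states, whereas liver worsening and a pSOFA increase are changes by name. Counting all randomised children by what happens after randomisation is clear and reproducible, and nothing in the SAP contradicts it. This stands: the choice between any occurrence and new onset is a choice of estimand. It is a reason to keep the present count and add to it.

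**Replacing the definition would also lose safety information.** A drug might prolong or worsen an abnormality that was already there, and those children would leave the comparison. This stands as well.

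**The size is unknown.** Prevalence, event rates and arm size are all assumed, and the effect measure for harms is not in the text at hand. If harms are reported as risk differences, the estimate hardly moves. This limits the point but does not remove it, because the loss of power in Step 3 does not depend on which measure is reported.

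**Stronger readings the document does not support.** A reader might infer that every harm ratio in the trial is pulled toward 1. Table S1 does not bear that out: liver function is measured from baseline, haemolysis and oxalate nephropathy are reported by the treating team, and infection must be hospital-acquired. Hyperglycaemia is defined by insulin treatment, and at most a child without diabetes already on intravenous insulin raises a similar question. A reader might also infer that an abnormal value at randomisation is enough to count. It is not, since both rows need a value after randomisation. Nor is this a bias between arms, because randomisation balances existing abnormalities on average.

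**Conclusion.** The point holds for two rows of Table S1 and as a loss of sensitivity and attribution. Hypernatraemia and hypoglycaemia carry no new-onset condition, so an abnormality that predates randomisation and persists is counted as an event.

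Dilution of the ratio rests on equal prevalence and equal persistence across arms. The ratios of 1.71, 1.49 and 1.31 against a true 2.00 mark the greatest dilution at each assumed prevalence, because they take every existing abnormality to persist. If almost no child is beyond the threshold at randomisation, the present wording costs almost nothing. If treatment changes persistence, the direction is open, and the present count alone cannot show which of the two effects is at work.

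These are secondary safety outcomes and the trial's main conclusion does not depend on them. The change is worth making before the data are analysed, because a new-onset analysis added afterwards would look like a choice made on the results.

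**What to change.** In Table S1, for both outcomes:

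1. Keep the present any-value count, by arm, among all randomised children.
2. Pre-specify a new-onset comparison: a first value beyond the threshold after randomisation, among children whose last pre-randomisation value was not beyond it. The condition uses only a pre-randomisation value, so the comparison within this group is still a randomised one.
3. List by arm the children who were already beyond the threshold.
4. State how a child with no pre-randomisation value is handled, and report the number of such children by arm.

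The cost is one derived variable per outcome and a slightly smaller denominator for the new-onset comparison. S5 says only that pre-determined biochemical variables are recorded, and the baseline table is not in the text at hand. If pre-randomisation sodium and glucose are not already captured, they would have to be extracted from the medical record.

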**S6. Listing of protocol deviations recorded for the RESPOND trial**

*Protocol deviations listed with a * contribute to exclusions applied to participants to determine the per-protocol cohort. ^#^ indicates protocol deviations will be reviewed on a case-by-case basis for applicability to per-protocol cohort selection.*

A consultant or investigator initiated withdrawal from the study prior to the finalisation of informed consent

Time taken to obtain informed consent exceeded 24 hours

Informed consent obtained but no study data collected

Informed consent obtained but patient was not ultimately randomised

Informed consent implemented / attempted but patient did not meet study specified inclusion / exclusion for enrolment in the study

*Patient randomised but there was no intention to treat

*Patient randomised but did not meet study specified inclusion / exclusion criteria for enrolment in the study

Patient randomised but informed consent was ultimately not obtained

*Patient randomised to an incorrect strata

*Patient randomised but did not receive / commence on any study treatment(s)

Patient randomised while study on hold

*First treatment received / commenced is not the same as the randomised allocation

*Study treatment not delivered according to protocol

*Patient randomised to "Vitamin C and Hydrocortisone" but did not receive Vitamin C

*Patient randomised to "Vitamin C and Hydrocortisone" but did not receive Hydrocortisone

*Patient randomised to "Hydrocortisone only" but received Vitamin C

*Patient randomised to "Hydrocortisone only" but did not receive Hydrocortisone

*Patient randomised to "Standard Care" but received Vitamin C

Protocol not followed for blood sampling

Baseline survey not provided by research coordinator

6-month follow-up not attempted by research coordinator

*Trial drugs continued >24 hours post ceased inotropes

*Clinical decision to cease trial drugs < 3 days while still being treated for septic shock

*^#^Protocol not followed

*^#^Other

**Figure S1.** Proposed participant flow diagram including long-term outcomes

[figure not shown]

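### The haemolysis outcome in Table S1 is filtered by an open-ended judgement of cause, which no other harm row shown there has

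*SAP*

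**What the plan says.** In the SAP's Table S1, haemolysis within 7 days is counted as follows: "As reported by the treating medical team within 7 days post-randomisation, and if not explained by other factors such as ECMO". The row gives no laboratory criterion, no closed list of excusing causes and no time limit on when such a cause must have begun. It names no judge and asks for no any-cause count alongside.

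The other harm rows in the table are built differently. Oxalate nephropathy also relies on the clinicians' report, but without a filter: "As reported by treating medical team within 28 days post-randomisation". Hypoglycaemia is a plain laboratory threshold: "Blood glucose level <2.6 mmol/L within 7 days post-randomisation". Hypernatraemia and liver function also use laboratory thresholds, hyperglycaemia is defined by insulin treatment, and hospital-acquired infection requires microbiological confirmation. None of these rows removes an event because something else might account for it.

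ECMO appears elsewhere in Table S1 as part of an outcome. Survival free of cardiovascular support is defined as "Duration of days alive and free from inotropes/vasopressors and ECMO, censored at 28 days post-randomisation", and survival free of organ support also includes ECMO.

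Section S6 shows three arms: vitamin C with hydrocortisone, hydrocortisone only, and standard care. One listed deviation is "Patient randomised to 'Standard Care' but received Vitamin C". The supplied text mentions no placebo.

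**The concern.** A harm comparison between randomised arms does not need each event to be assigned a cause. Causes unrelated to treatment are expected to arise equally often in each arm, so comparing all events by arm already allows for them. Filtering events by presumed cause adds a second step that need not behave the same way in each arm.

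The two steps can diverge by two routes. The first is judgement: someone who knows the allocation may be readier to accept another explanation in one arm than in another. The second needs no knowledge of allocation. If ECMO is used more in one arm after randomisation, even a mechanical application of the rule removes more events from that arm. In either case a real excess of haemolysis could be hidden, or an apparent one created.

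**Working it through.** **The plan's own figures.** No event rate, power or significance level is attached to this outcome in the supplied text, so there is no figure to reproduce. What follows is an illustration, and all its rates are assumed.

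**Inputs.** Let p be the any-cause haemolysis risk in an arm and q the share of those events set aside as otherwise explained. I take p = 6% in both arms (no true effect), and then 6% v 9% (true risk ratio 9/6 = 1.50). For q I take equal shares of 20%, and unequal shares of 10% and 40% in each direction.

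**Formulas.** Counted risk = p × (1 − q). With subscripts V for vitamin C and C for control:

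counted risk ratio = (p_V / p_C) × (1 − q_V) / (1 − q_C)

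The second factor is the distortion. It does not depend on the assumed event rate, only on how far the shares set aside differ.

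| Any-cause risk, C v V | Share set aside, C v V | Counted risk, C v V | Risk ratio |
|---|---|---|---|
| 6% v 6% | 20% v 20% | 4.8% v 4.8% | 1.00 |
| 6% v 6% | 10% v 40% | 5.4% v 3.6% | 0.67 |
| 6% v 6% | 40% v 10% | 3.6% v 5.4% | 1.50 |
| 6% v 9% | 20% v 20% | 4.8% v 7.2% | 1.50 |
| 6% v 9% | 10% v 40% | 5.4% v 5.4% | 1.00 |
| 6% v 9% | 40% v 10% | 3.6% v 8.1% | 2.25 |

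For example, in the second row 0.06 × 0.9 = 5.4%, 0.06 × 0.6 = 3.6%, and 3.6/5.4 = 0.67.

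**Reading the table.** With equal shares the ratio is right, and the only cost is the fifth of events lost. With shares of 10% and 40% the ratio is multiplied by 0.6/0.9 = 0.67 or by 0.9/0.6 = 1.50. That is enough to erase a true ratio of 1.50 or to produce one where there is none.

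**The case against.** The strongest reply is that the clause is a deliberate choice of specificity. ECMO circuits can cause haemolysis whatever drug is given. Adding the same background risk to both arms leaves the risk difference unchanged but pulls a true ratio towards 1. ECMO is also the one excusing factor the row names, so it leaves the least room for discretion. These points are fair. They support showing a filtered count, but not making it the only count. They also do not cover the unnamed other factors, or a difference in ECMO use between arms.

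A second reply is that the main text is not shown. The S3 checklist places harms on page 15, S5 says adverse events are recorded from the clinical record, and the S4 charter sends associated adverse events to the DSMB. An excluded haemolysis may therefore still be captured as an adverse event with its attribution. This can be neither confirmed nor ruled out. It would soften the point, but the Table S1 outcome would still be the filtered one.

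A reader might also infer several things that the documents do not support:

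- That the treating team makes the judgement and knows the allocation. The row says the team reports haemolysis. It does not say who decides that another cause explains it, although the team is the natural reading. The arm names in S6, with no placebo mentioned, suggest open treatment but do not establish it. The masking language in S4 concerns what the DSMB sees.
- That patients are excluded after randomisation. The clause drops events, not participants.
- That ECMO always follows randomisation. Table S1 counts ECMO time after randomisation, but ECMO may already have been running.

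**Conclusion.** The point holds as a minor one. Haemolysis is the only harm row shown in Table S1 that discards reported events on an open-ended judgement of cause, and the row states neither who decides nor whether that person is blinded. Bias follows only if attribution or ECMO use differs by arm. In that case it can run in either direction, and otherwise the loss is of events alone. The ratios of 0.67 and 1.50 show the mechanism under assumed shares of 10% and 40%. They do not estimate what has happened in this trial, and no rate in the documents allows such an estimate.

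It would also go too far to call an all-cause count unbiased. That count still depends on whether the treating team reports haemolysis at all, which knowledge of allocation could influence. It removes one source of possible bias and leaves the other.

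**What to change.** In Table S1, make the main haemolysis outcome every event reported within 7 days of randomisation, by randomised arm and irrespective of attributed cause. Beneath it, as secondary lines, show the count under the present rule and each event's ECMO status, noting whether ECMO began before or after randomisation. State who makes the attribution and whether that person is blinded. Nothing in the present definition is lost, because its count is still reported.

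The wording change is small, but there are two costs. The main count will include background events from ECMO circuits, which may dilute a true ratio; the secondary lines let a reader see how much. If sites applied the clause at data entry, events judged to be explained may not be in the dataset. Existing adverse-event or source records would then need checking, and S5 says records are locked once monitoring is finalised, so some might have to be reopened.

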**S2. List of approved protocol modifications**

| **Version Number and Date** | **Ethics Committee Approval Date** | **List of Modifications** |
| --- | --- | --- |
| *1.0* | *-* | *Original submission* |
| 1.1 | 11/12/2020 | - Process to follow in case of enrolment of oncology patients - Time frame for obtaining consent to continue must not exceed 24 hours (previously 72 hours). |
| 1.2 | 04/03/2021 | - Study exclusion criteria updated to remove “Patients with known or suspected scurvy” - Research Coordinator changed - New RESPOND generic email address - Randomisation updated to reflect new computer-based randomisation process - Small grammatical errors corrected throughout |
| 1.3 | 06/05/2021 | - ANZCTR number added - Additional secondary outcomes added: (1) Neurodevelopmental vulnerability at 6 months post sepsis, (2) new onset AKI - Randomisation process updated, with new screenshot included to outline the electronic based method |
| 1.4 | 01/06/2021 | - Chronic renal failure removed from exclusion criteria - Addition of clinical staff to the randomisation process - Site investigator list updated - Study management committee updated |
| 1.5 | 17/09/2021 | - Primary outcome changed to time alive free of vasopressors censored at 7 days - Thiamine removed from the intervention - PedsQL added to baseline observations. - Consumer representative added - Study sites in Brazil added |
| 1.6 | 01/09/2022 | - Additional investigator added - Amended Figure 3 on page 25 – study procedures - Investigators title change - Additional safety features and interim analysis plan - Added exclusion medications - cyanocobalamin or Deferoxamine for their co-morbid conditions - Included Sponsor/Updated Funding and duration of trial - Updated current literature - Amended follow up process - Amended DSMB Roles and Responsibilities |
| 1.7 | 08/11/2024 | - Update to Trial Steering Committee composition - Inclusion of Indian sites and investigators - Amended timeframes hospital-acquired microbiologically confirmed infection - Updated long-term follow-up processes |

ANZCTR Australian New Zealand Clincial Trials Registry; AKI acute kidney injury; PedsQL Pediatric Quality of Life Inventory; DSMB Data Safety Monitoring Board

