|  | 26c | any calculation or transformation used to derive the outcome (e.g., change from baseline, QoL score, time to event, logarithm, etc) | Supplementary Table S1 |
| Analysis methods | 27a | what analysis method will be used and how the treatment effects will be presented | 11-13 |
|  | 27b | any adjustment for covariates | 11-12 |
|  | 27c | methods used for assumptions to be checked for statistical methods | 12 |
|  | 27d | details of alternative methods to be used if distributional assumptions do not hold, e.g., normality, proportional hazards, etc | 12 |
|  | 27e | any planned sensitivity analyses for each outcome where applicable | 13 |
|  | 27f | any planned subgroup analyses for each outcome including how subgroups are defined | 12 |
| Missing data | 28 | Reporting and assumptions/statistical methods to handle missing data (e.g., multiple imputation) | 13 |
| Additional analyses | 29 | Details of any additional statistical analyses required, e.g., complier-average causal effect10 analysis | 13 |
| Harms | 30 | Sufficient detail on summarising safety data, e.g., information on severity, expectedness, and causality; details of how adverse events are coded or categorized; how adverse event data will be analysed, i.e., grade 3/4 only, incidence case analysis, intervention emergent analysis | 15 |
| Statistical software | 31 | Details of statistical packages to be used to carry out analyses | 15 |
| References | 32a | References to be provided for nonstandard statistical methods | N/A |
|  | 32b | Reference to Data Management Plan | Supplementary Material S6 |
|  | 32c | Reference to the Trial Master File and Statistical Master File | N/A |
|  | 32d | Reference to other standard operating procedures or documents to be adhered to | N/A |

CONSORT, Consolidated Standards of Reporting Trials; hbA_1c_, haemoglobin A_1c_; QoL, quality of life; SAP, statistical analysis plan

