**S5. Description of data sources and data monitoring plan for the RESPOND trial**

**DATA SOURCES**

Two data sources are being used for data collection:

- Clinical record: Data are recorded from the patient hospital medical record including demographic variables, comorbid status, type of infection, severity at baseline, primary endpoints, secondary endpoints, pre-determined physiological, biochemical and microbiological variables of interest, safety, and long-term outcome measures. Administration of study drugs, duration, doses, amount of drug received, adverse events, protocol deviations and reason for protocol violations are also recorded; and
- Parent-completed follow-up questionnaires: Parent-reported screening questionnaires using validated tools collect child and parent outcomes. Questionnaires are completed at baseline and six months post-randomisation.

Data from both sources are collected into the purpose-built study database developed in Research Electronic Data Capture (REDCap), hosted by The University of Queensland (1, 2), by direct entry. The follow-up questionnaires for collecting long-term outcome measures are administered by a secure web link provided to parents in an email, with responses collected in the study database. In the case of parent comorbidity or circumstances limiting completion of the online screeners, questionnaires will be administered via telephone interview by the site Research Coordinator.

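### Children with a 6-month Functional Status Score but no baseline score are left out of the between-arm comparison, which loses information without reducing bias if baseline missingness is unrelated to arm

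*SAP*

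**What the plan says.** The functional-status row of SAP Table S1 has two components. The first is "Change in Functional Status Score (FSS) from baseline to 6 months post-randomisation". For this component the row adds that "Participants without a recorded FSS at baseline but who have a score at 6 months will not be included" when the outcome is calculated, "but will have their 6 month FSS reported descriptively". The second component, the modified Paediatric Overall Performance Category at 6 months, has no baseline requirement.

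The text at hand names no all-data alternative or sensitivity analysis for FSS. The neurodevelopmental outcome in the same table does have a sensitivity analysis for incomplete assessments.

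Section S5 (Data sources) says "Questionnaires are completed at baseline and six months post-randomisation", and section S6 lists "Baseline survey not provided by research coordinator" among the recorded deviations. Neither place says whether FSS belongs to that survey.

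**The concern.** The wording on exclusion is an explicit rule, not a gap left to another document. It makes the baseline score a condition for entering the between-arm comparison. Randomisation does not require that: the arm difference in change and the arm difference in 6-month score adjusted for baseline estimate the same effect, and baseline serves only to improve precision. A child whose 6-month score is known carries information on that effect with or without a baseline.

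At stake is the width of the confidence interval for one long-term outcome. The two functional-status components may also be compared on different sets of children.

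**Working it through.** The plan gives no figure for this outcome, so there is none to reproduce.

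**Inputs, all assumed.** Share of children with a 6-month FSS but no baseline: m = 10–30%. Correlation between baseline and 6-month FSS: r = 0.5 or 0.7, with 0.9 as a limit. Equal variances at the two times, 6-month variance set to 1, and missingness unrelated to arm.

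**Relative variance of an arm difference**

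- A. Change score, complete cases, no baseline adjustment: 2(1 − r)/(1 − m)
- B. Baseline-adjusted, complete cases: (1 − r²)/(1 − m)
- C. Baseline-adjusted, all children with a 6-month score, missing baseline set to an arm-blind mean plus indicator, ordinary least squares: (1 − m)(1 − r²) + m

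B/C is the cost of the exclusion alone. A/C adds the cost of an unadjusted change score.

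| r | m | A | B | C | B/C | A/C |
|---|---|---|---|---|---|---|
| 0.5 | 10% | 1.000/0.9 = 1.111 | 0.75/0.9 = 0.833 | 0.9×0.75 + 0.1 = 0.775 | 1.08 | 1.43 |
| 0.5 | 30% | 1.000/0.7 = 1.429 | 0.75/0.7 = 1.071 | 0.7×0.75 + 0.3 = 0.825 | 1.30 | 1.73 |
| 0.7 | 10% | 0.600/0.9 = 0.667 | 0.51/0.9 = 0.567 | 0.9×0.51 + 0.1 = 0.559 | 1.01 | 1.19 |
| 0.7 | 30% | 0.600/0.7 = 0.857 | 0.51/0.7 = 0.729 | 0.7×0.51 + 0.3 = 0.657 | 1.11 | 1.30 |

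**The filling method matters at high correlation.** C gives children with and without a baseline the same residual variance. At r = 0.9 and m = 10%, C = 0.9×0.19 + 0.1 = 0.271, which is worse than B = 0.19/0.9 = 0.211 and A = 0.2/0.9 = 0.222. C stops beating B once 1 − r² falls below (1 − m)/(2 − m): r of about 0.73 at m = 10% and 0.77 at m = 30%.

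Weighting the two groups by their own precision gives 1/[(1 − m)/(1 − r²) + m], which never exceeds B. At r = 0.9 and m = 10% it is 1/(0.9/0.19 + 0.1) = 0.207. Multiple imputation with many imputations has variance of about (1 − r²)[(1 − r²) + r²/(1 − m)], which also never exceeds B: here 0.19×(0.19 + 0.81/0.9) = 0.207. So the excluded children always carry information, but simple mean filling does not always recover it.

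**Bias, by simulation** (4,000 replicates, n = 200, r = 0.5, about 20% missing, true effect 0.3)

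| Baseline missingness | A | B | C |
|---|---|---|---|
| completely at random | 0.000 | 0.001 | 0.001 |
| depends on baseline severity | −0.004 | −0.004 | −0.003 |
| depends on baseline in one arm only | 0.086 | −0.002 | 0.069 |
| depends on 6-month outcome in one arm only | −0.092 | −0.137 | 0.029 |

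In the first scenario the standard deviations of the estimates were 0.158 (A), 0.138 (B) and 0.127 (C). When missingness is unrelated to arm, the exclusion removes no bias because there is none. When it differs by arm, C was less biased than A in both scenarios, but neither B nor C was always the better.

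**The case against.** **The analysis model is not visible.** The S3 checklist places analysis methods, "any adjustment for covariates" and missing-data handling on pages 11–13 of the main SAP, which are not at hand. If those pages adjust change for baseline FSS in a linear model, the treatment estimate is the same as from the 6-month score adjusted for baseline, and the change-score penalty vanishes. This stands. A reader might take 1.43–1.73 as the cost of the plan, but it holds only without that adjustment.

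**Equal variances are assumed.** If the baseline SD is k times the 6-month SD, the unadjusted change score has excess variance (k − r)² over the adjusted analysis. That is never negative, but it is zero at k = r. A reader might infer that change scores lose whenever the correlation is below 1; this is not so in general.

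**The scores are not discarded.** They are described, and the same children can contribute to the second functional-status component. This is correct. What is lost is their contribution to the FSS comparison.

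**Stronger readings lack support.** A reader might infer that the rule breaks intention-to-treat, that missing baselines concentrate in emergency enrolments, or that the survey deviation shows many FSS baselines are missing. The document gives no rate or pattern of missing FSS baselines and does not tie FSS to the survey. S5 also names the clinical record as a source of long-term outcomes. The rule is a prespecified complete-case restriction on one outcome, and the accurate statement is that randomised children with known 6-month scores are left out of one comparison.

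None of this supplies a reason for the exclusion itself.

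**Conclusion.** The point holds as a minor one. Table S1 keeps observed 6-month outcomes out of the FSS comparison by rule, and the text at hand offers no alternative analysis that uses them. With 10–30% of baselines missing, equal variances and the ordinary least-squares comparison, the exclusion alone costs a variance factor of about 1.08–1.30 at r = 0.5 and 1.01–1.11 at r = 0.7. Only if change is also compared without baseline adjustment does this become 1.43–1.73 and 1.19–1.30.

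The true size is unknown and may be negligible. At 5% missing and r = 0.9 even the unadjusted change score keeps 94% of the information in the precision-weighted all-data analysis. The statement that no bias is reduced rests on baseline missingness being unrelated to arm.

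**What to change.** In Table S1, make the 6-month FSS the outcome, adjusted for baseline FSS, and include every child with a 6-month score. Handle a missing baseline by multiple imputation, with the 6-month score and arm in the imputation model. Arm-blind mean imputation plus a missing indicator is a simpler choice if the correlation is not high; above roughly 0.7 the residual variance should then differ between children with and without a baseline. Keep the complete-case change score as a sensitivity analysis, and report the number of missing baselines by arm.

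The cost is a short edit and slightly more analysis work, with no new data. The downside is that the filled-in analysis is safest when baseline missingness does not depend on arm, which the counts by arm would help to judge. If the main SAP text already adjusts for baseline, only the exclusion sentence needs to change.
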